#### Optional additional text-messages for smoking cessation (MCT + and MCT)

Participants who intend to stop smoking (intenders and actors according to the HAPA) will be offered the option of receiving additional text-messages for quit-day preparation and relapse prevention. Program participants in these stages will be informed about this option biweekly. After entering a scheduled quit date, the program will provide up to two daily text messages (weeks –1 to +1: two daily text messages; weeks +2 and +3: one daily text message). E.g., ‘Good evening, Marc. Tomorrow’s going to be your first smoke-free day. It would be best for you to throw away all cigarettes, ash trays, and lighters today. Try avoiding boredom tomorrow. Buy some gum for tomorrow in advance.’

### Outcomes

The primary outcome measures assessed at the 6-months follow-up are: (1) 7-day point prevalence smoking abstinence (i.e. not having smoked a puff within the past 7 days), (2) cigarette consumption (number of cigarettes smoked on a typical day for daily smokers, typical number of smoking days per month, and number of cigarettes smoked on a typical smoking day for occasional smokers).

Secondary outcome measures, assessed at the 6-months follow-up include: (1) 30-day point prevalence smoking abstinence (i.e. not having smoked a puff within the past 30 days), (2) stage of change according to the HAPA [10], (3) a quit attempt within the 6-month period, (4) alcohol consumption assessed by a 7-day drinking calendar, for which participants would need to think about a typical week in the month prior to assessment and recall the number of standard drinks they typically consumed for each day.

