## Methods and design

### Design and hypotheses

A two-arm cluster-randomised trial will be conducted to test the efficacy of the *MCT*, a text messaging-based intervention for smoking cessation for young people compared to the *MCT+*, a combined web- and text messaging-based integrated smoking cessation and alcohol intervention. Study participants will be assessed at the baseline and at a 6-month follow-up (Figure 1). Our main hypothesis is that the integrated intervention will be more effective than the smoking cessation only intervention for reducing cigarette consumption and achieving smoking abstinence.

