**Study design.**

### Participants, setting, and procedure

The interventions will be tested on vocational school students due to the high smoking prevalence in this population (approximately 42% of the Swiss sample were daily or occasional tobacco smokers) [11]. The Cantonal Office for Secondary Education in Zurich and further prevention specialist centres in other Swiss Cantons will request teachers from vocational schools to allow researchers to conduct the Internet- and text messaging-based smoking cessation program with some of their students. Participating teachers will schedule 30 minutes per class for eligibility screening, obtaining informed consent, and collect baseline data.

Study assistants (graduate students of psychology or prevention specialists) will recruit study participants by inviting all vocational school students from a school class to participate in an online health survey during a regular school lesson. Furthermore, they will inform students that some would be invited to participate in a study testing the efficacy of a text messaging intervention for health promotion. To decrease reporting bias, the study assistants will not provide further information about the purpose of the study until the completion of the eligibility screening. This online screening includes data collection on demographics, alcohol consumption, weekly physical activity, smoking status, and mobile phone ownership. Inclusion criteria are: (1) daily or occasional cigarette smoking (at least 4 cigarettes in the preceding month and at least one cigarette during the preceding week) and (2) ownership of a mobile phone.

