### Data analyses

We will use regression models to compare the efficacy of the interventions on the different outcome measures. If necessary, we will control for baseline differences by entering additional baseline variables as covariates to the regression models. All analyses will be performed considering the intention-to-treat principle. Given the clustered nature of the data (students in different classes), we will compute robust variance estimators for all regression analyses.

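### The primary outcome of cigarette consumption is listed as different items for daily and occasional smokers, with no single common variable and no statement of when smoker class is determined

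*Protocol article*

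**What the plan says.** Under Outcomes, the protocol article introduces two primary measures with the words "The primary outcome measures assessed at the 6-months follow-up are". The first is 7-day abstinence. The second is cigarette consumption, described in parentheses by one item for daily smokers and two for occasional smokers. The list begins "number of cigarettes smoked on a typical day for daily smokers, typical number of smoking days per month", and the part for occasional smokers reads in full "typical number of smoking days per month, and number of cigarettes smoked on a typical smoking day for occasional smokers". No rule joins the three items.

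The trial enrols both kinds of smoker: "daily or occasional cigarette smoking (at least 4 cigarettes in the preceding month and at least one cigarette during the preceding week". Design and hypotheses states one consumption hypothesis for all of them, that "the integrated intervention will be more effective than the smoking cessation only intervention for reducing cigarette consumption and achieving smoking abstinence".

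Under Data analyses the article says "We will use regression models to compare the efficacy of the interventions on the different outcome measures" and "All analyses will be performed considering the intention-to-treat principle". Baseline variables are to be added as covariates only where this is judged necessary, and robust variance estimators will allow for clustering by class. Participants, setting, and procedure records that baseline consumption is collected per day or per week.

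**The concern.** A single hypothesis needs a single quantity to test. Here a daily smoker contributes cigarettes per day, and an occasional smoker contributes a count of days and a count per smoking day. Smoker class is also something both programmes aim to change. Someone who has cut down to a few days a month has no natural answer to the daily-smoker item at follow-up, so the items may sort people by their current status. If each item were then compared between arms among those who answered it, the comparison would no longer be between the groups as randomised. Participants for whom the programme worked best would drop out of the daily-smoker comparison.

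The baseline measure is in yet another format (per day or per week), so adjusting for it also needs a stated conversion. Leaving that adjustment conditional makes the model for a primary outcome depend on the data observed.

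**Working it through.** **The plan's own figures.** The article gives no mean, standard deviation or effect size for consumption, so there is no consumption figure to reproduce. The sample size rests on abstinence alone (12% against 18%, two-sided 5%, 80% power). A two-proportion formula with continuity correction gives 588 per group, as stated. With the design effect 1 + (4 − 1) × 0.05 = 1.15, 588 × 1.15 = 676.2, against the stated 675. Nothing below changes the sample size.

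**How many participants the listed items may miss.** On the plan's assumed abstinence rates and 675 per group:
- Smoking cessation only: 0.12 × 675 = 81
- Integrated: 0.18 × 675 = 121.5, about 122

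Up to this many would be neither daily nor occasional smokers at follow-up. The true number without an obvious item is smaller, because some 7-day abstainers will have smoked earlier in the month.

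**What a split by follow-up status could do.** All consumption values here are assumptions. Take daily smokers at baseline, half light and half heavy. In the smoking cessation only arm nothing changes. In the integrated arm some become occasional smokers at 12 days per month and 5 cigarettes per smoking day, which is 12 × 5 / 30 = 2 per day on average.

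With light = 8 and heavy = 16 per day, and 10% of daily smokers moving, all from the lighter half:
- Smoking cessation only arm, either way: 0.5 × 8 + 0.5 × 16 = 12.00
- Integrated arm, those still daily: (0.4 × 8 + 0.5 × 16) / 0.9 = 12.44, a difference of +0.44
- Integrated arm, everyone on one scale: 0.4 × 8 + 0.5 × 16 + 0.1 × 2 = 11.40, a difference of −0.60 per day, or −0.60 × 30 = −18 cigarettes per month

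If the same 10% come from the heavier half:
- Those still daily: (0.5 × 8 + 0.4 × 16) / 0.9 = 11.56, a difference of −0.44
- Everyone on one scale: 0.5 × 8 + 0.4 × 16 + 0.1 × 2 = 10.60, a difference of −1.40

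The same formulas with other assumptions (differences are integrated minus smoking cessation only, in cigarettes per day):

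| Light / heavy per day | Who moves | Share of daily smokers moving | Among those still daily | Common scale, all |
|---|---|---|---|---|
| 10 / 14 | lighter | 5% | +0.11 | −0.40 |
| 5 / 20 | lighter | 5% | +0.39 | −0.15 |
| 8 / 16 | lighter | 10% | +0.44 | −0.60 |
| 10 / 14 | lighter | 20% | +0.50 | −1.60 |
| 5 / 20 | lighter | 20% | +1.88 | −0.60 |
| 12 / 12 | either | 10% | 0.00 | −1.00 |
| 8 / 16 | heavier | 10% | −0.44 | −1.40 |

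The split therefore reverses the sign when lighter smokers move, hides the benefit when consumption is uniform, and understates it in the heavier-mover case. If equal shares of the same kind of smoker move in both arms, the difference between arms is zero on either measure. If class is fixed at baseline and the items are converted to one unit, nobody leaves the comparison.

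**The case against.** The strongest reply is that the article names one outcome and merely lists the questions that measure it. The two occasional-smoker items are exactly what is needed to calculate a quantity comparable with cigarettes per day, so a conversion may well be intended. The Background reports the predecessor trial's consumption result as a single mean number of cigarettes per day, and the intention-to-treat commitment argues against dropping people who change class. A full plan that is not shown may settle the coding and the model.

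Much of this stands. A reader might infer that the trial will compare means among continuing daily smokers, that it breaks its intention-to-treat principle, or that its result will be reversed. The article supports none of these. It nowhere plans a mean among those still smoking daily or an analysis split by follow-up status. Reversal further requires that mainly lighter smokers move and that more of them do so in one arm, although both arms receive the smoking programme. The choice of model family can fairly be left to the analysis plan.

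What the reply does not remove is that the article does define the primary outcome, and as defined it is not one variable. The time at which class is determined is left open for a characteristic that the interventions aim to change. The wording admits analyses that can differ in sign.

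**Conclusion.** The concern holds as a defect in the definition of a primary outcome: there is no common consumption variable, no statement whether smoker class is baseline or follow-up status, and only conditional adjustment for baseline. It is not shown that a biased analysis is planned.

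If the items were analysed by follow-up status, the comparison would be exposed to selection after randomisation. With lighter daily smokers moving in the integrated arm only (5% to 20% of daily smokers, light/heavy values from 10/14 to 5/20), the difference among those still daily runs from +0.11 to +1.88 cigarettes per day against that arm. The common-scale difference runs from −0.15 to −1.60 in its favour. These ranges rest entirely on assumed consumption values and on movement in one arm only. They show that the choice of definition can matter, not how large the effect would be in this trial. The abstinence outcome and the sample size are unaffected. The point is worth correcting because the remedy costs almost nothing.

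**What to change.** In Outcomes, define one variable for all randomised participants, cigarettes per typical month at 6 months:
- daily smokers: 30 × cigarettes per typical day
- occasional smokers: smoking days per month × cigarettes per smoking day
- 0 only for those who smoked nothing over that month

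Zero should not be given to everyone who is 7-day abstinent, since such a person may have smoked earlier in the month. The 30-day abstinence question, already a secondary outcome, can help identify the true zeros.

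In Data analyses, state that this outcome is always adjusted for baseline consumption in the same unit (30 × daily, or 30/7 × weekly consumption) instead of only when needed. Keep the class-robust variance. Base any daily/occasional subgroups on baseline status. The model should suit zeros and skewed counts, but its family may be left to the analysis plan.

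The cost is a few sentences. The items are already listed for collection. The one practical check is that the telephone interview puts the two occasional-smoker questions to anyone who is abstinent for 7 days but not for 30.

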### Data analyses

We will use regression models to compare the efficacy of the interventions on the different outcome measures. If necessary, we will control for baseline differences by entering additional baseline variables as covariates to the regression models. All analyses will be performed considering the intention-to-treat principle. Given the clustered nature of the data (students in different classes), we will compute robust variance estimators for all regression analyses.

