Subsequently, study assistants will provide the eligible candidates with information about the study aims, interventions, assessments, reimbursement, and data protection, both online and in paper form. Reimbursement of 10 Swiss Francs (~ € 8.00) for participation at the 6-month follow-up assessment will be offered to all study participants. Moreover, participants will be offered 0.5 Swiss Franc (~ € 0.40) for responding to each of the 11 weekly SMS assessments conducted during the program. After obtaining informed consent online, all study participants will be requested to choose a username and provide their mobile phone number. Furthermore, the following smoking related variables will be assessed: intention to quit, daily/weekly cigarette consumption, previous cessation attempts, number of friends who smoke, age at smoking onset, smoking cessation outcome expectancies, situations in which craving for cigarettes occur, alternative strategies to handle these craving situations, and cost per pack of cigarettes. The integrated smoking cessation and alcohol intervention participants will receive additional questions on typical drinking days and times that are necessary for tailoring the intervention content. Computer assisted telephone interviews will be conducted by trained interviewers at the 6-month follow-up assessment.

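### Covariate adjustment depends on observed baseline differences, so chance picks the primary model; prespecified prognostic covariates would serve better at no cost

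*Protocol article*

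**What the plan says.** The Data analyses section opens with "We will use regression models to compare the efficacy of the interventions on the different outcome measures" and then sets the covariate rule: "If necessary, we will control for baseline differences by entering additional baseline variables as covariates to the regression models". It gives no variable, no threshold and no time for the decision. The rule covers the models for all outcomes, so it applies to both primary outcomes listed under Outcomes: 7-day point prevalence abstinence and cigarette consumption at 6 months. Clustering by class is handled separately: "we will compute robust variance estimators for all regression analyses".

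Under Participants, setting, and procedure, the baseline items asked of every participant include "intention to quit, daily/weekly cigarette consumption, previous cessation attempts, number of friends who smoke, age at smoking onset". The eligibility screening before that covers "data collection on demographics, alcohol consumption, weekly physical activity, smoking status, and mobile phone ownership". Participants may be daily smokers or occasional smokers with as little as "at least 4 cigarettes in the preceding month and at least one cigarette during the preceding week". Under Randomisation and allocation concealment, classes are randomised from a separate list for each school, and participants learn their group only after giving consent and baseline data.

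**The concern.** Because allocation is randomised and is concealed from participants and supervising assistants during the baseline assessment, differences between the arms should be due to chance. A rule that responds to those differences lets chance choose the model. It also selects covariates on the wrong ground. A covariate earns its place by predicting the outcome, and it does so whether or not it is balanced.

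This trial already holds strong candidates. Cigarette consumption is measured at baseline and is itself a primary outcome, and the eligible range of smoking is wide. If baseline smoking enters only when it differs between arms, most of the precision it could provide is lost in most trials. A further issue is that the trigger is undefined, so two analysts could follow the same sentence and reach different primary models.

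**Working it through.** **The plan's own figures.** For 12% against 18%, two-sided α = 5% and 80% power, the chi-square formula with continuity correction gives 588 per group, as stated (555 without the correction). The design effect is 1 + (4 − 1) × 0.05 = 1.15, and 588 × 1.15 = 676.2 against the stated 675. The effective size is 675 / 1.15 = 587 per arm. The sample size is not in dispute.

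**Assumptions not in the article.** 'Necessary' means p<0.05 in a test of one baseline covariate. The baseline/follow-up correlation r is 0.3, 0.5 or 0.7. The effect on consumption has 80% power unadjusted. Large-sample normal statistics are used, with clustering absorbed into the effective size.

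**Method for consumption.** Let Zx be the standardised baseline difference between arms and Zy the unadjusted test statistic, with correlation r.
- With 80% unadjusted power, Zy has mean 1.960 + 0.842 = 2.802.
- The adjusted statistic is (Zy − r·Zx) / √(1 − r²). It is independent of Zx and has mean 2.802 / √(1 − r²).
- Power when always adjusting is Φ(2.802/√(1 − r²) − 1.960).
- Power under the conditional rule is 0.95 × P(|Zy| > 1.960 given |Zx| ≤ 1.960) + 0.05 × (power when always adjusting).

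At r = 0.5, always adjusting gives Φ(3.235 − 1.960) = 89.9%. The conditional rule gives 0.95 × 0.8067 + 0.05 × 0.8989 = 81.1%. With no true effect, the conditional rule rejects with probability 0.95 × 0.0429 + 0.05 × 0.05 = 4.3%.

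| r | Unadjusted power | Conditional rule | Always adjusted | Type I error, conditional | Unadjusted n per arm with same precision, 675 × (1 − r²) |
|---|---|---|---|---|---|
| 0.3 | 80.0% | 80.4% | 83.6% | 4.8% | 614 |
| 0.5 | 80.0% | 81.1% | 89.9% | 4.3% | 506 |
| 0.7 | 80.0% | 82.0% | 97.5% | 3.6% | 344 |

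The last column applies to the always-adjusted analysis: adjusting with that many per arm matches an unadjusted analysis of 675. At r = 0.5 the conditional rule forgoes (89.9 − 81.1) / (89.9 − 80.0) = 89% of the available gain, and the share is about the same at the other two values. Always adjusting keeps type I error at 5.0%.

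**Abstinence.** Logistic regressions were simulated at 588 per arm, 12% against 18%, with 4,000 trials per setting. The odds ratio per standard deviation of the covariate is again an assumption.

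| Odds ratio per SD | Unadjusted | Conditional rule | Always adjusted | Gain over conditional rule |
|---|---|---|---|---|
| 1.5 | 82.0% | 82.2% | 82.9% | 0.7 points |
| 2.0 | 81.8% | 82.2% | 84.1% | about 2 points |
| 2.5 | 82.5% | 83.1% | 86.7% | 3.6 points |

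**Choosing after seeing results.** If an analyst could take either the adjusted or the unadjusted consumption result, whichever was significant, type I error with one covariate would be about 6.4%, 7.3% and 8.3% at r = 0.3, 0.5 and 0.7.

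**The case against.** Four objections carry weight.

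- **'Additional' may refer to a base model that already holds baseline values.** The Background describes the predecessor trial's consumption result as a decrease from baseline to follow-up, so a baseline-referenced analysis is plausible here too. A reader might infer that baseline smoking is definitely left out. The article does not say so, and the loss shown for consumption applies only if it is. What stands is that no base model is named.
- **False positives do not increase under a fixed baseline trigger.** A reader might infer an inflated type I error, but the rule as modelled is conservative. Inflation needs a choice made after outcome results are seen. Baseline data are complete about six months before the outcome, so the decision could be taken without outcome data. The text neither states nor excludes a later choice.
- **Abstinence, the outcome that sets the sample size, loses little.** This is correct, and the large loss is confined to consumption.
- **A condensed article leaves the covariate list to the analysis plan.** This is fair for the list and the threshold. It does not answer the point, because the article states the principle, and a more precise imbalance trigger would still be an imbalance trigger.

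**Conclusion.** The point stands as a defect in a stated rule. Adjustment in both primary models depends on observed baseline differences, which under this design should be chance. For cigarette consumption the rule yields 80% to 82% power where prespecified adjustment would give about 84% to 97%. That rests on the assumed correlations of 0.3 to 0.7, a p<0.05 trigger, 80% unadjusted power, and a base model without baseline consumption. For 7-day abstinence the difference is about 1 to 4 points over assumed odds ratios of 1.5 to 2.5.

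The documents do not support the stronger claims that the trial's false-positive rate is inflated, that the model will be chosen after outcomes are known, or that power for abstinence is seriously reduced. The change is worth making because it is free. The plan is not invalid without it.

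**What to change.** Delete the conditional sentence. Before any outcome data are compared by arm, prespecify a short set of covariates that enters both primary models whatever the observed balance:

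- baseline cigarette consumption, or daily/occasional status;
- intention to quit;
- school, as the randomisation stratum, by fixed or random effect, with small schools pooled.

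Sex and age are optional. Keep the robust variance for classes, and report the unadjusted model as a sensitivity analysis. If a base model is already intended, naming its covariates meets the same need.

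The cost is a change of wording in the protocol or analysis plan. The smoking items are already collected from all participants before they learn their group, and school is known from the randomisation lists. The sample size and data collection do not change.

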## Discussion

This study protocol presents the design of a cluster randomised controlled trial comparing the smoking cessation efficacy of an integrated smoking cessation and alcohol intervention and a smoking cessation only intervention. Beyond the interventions’ efficacy, we also pay close attention to their retention rates since intervention intensity and complexity is higher in the integrated intervention than in the smoking cessation only intervention. This may result in different dropout rates; however, we do not have a clear directional hypothesis for attrition. Additionally, we will determine the acceptability of the interventions using objective markers, such as the number of views for the video clips that were integrated into the text messages.

As two major risk factors, tobacco smoking and alcohol consumption, are addressed simultaneously for one intervention group, the study could significantly add to the current knowledge of multiple behaviour change interventions [28].

Compared to face-to-face interventions, counselling via Internet and text messaging is economical and matches the lifestyle and communication habits of young people. Furthermore, while the costs of face-to-face counselling interventions significantly increase with an increase in intensity, they do not substantially increase in automated ICT-based interventions, provided the programs have been already developed. Therefore, since integrated intervention approaches are potentially more effective, they could be used with large groups of adolescents and young adults, e.g. in schools or workplaces, with only marginally higher costs compared to the smoking cessation only intervention.

